### Data Security and Analysis

Data will be entered directly in a database and kept in a secure network computer in a locked office at the Hiroshima University. All information will be uniquely anonymized. The operational process of this study will be subject to annual monitoring, and no audit is required. The occurrence of serious adverse events will be reported to the Certified Review Board of the Hiroshima University Hospital or the Ministry of Health, Labor and Welfare of Japan. Raw data from measurements will be analyzed using customized software that was independently developed to control the operation of the detector. Statistical analysis will be performed using the R statistical software (R Foundation for Statistical Computing) environment.

## Results

Recruitment began in November 2018 and was completed by March 2020. We expect to submit the results for publication by summer 2021.

## Discussion

### Overview

Some microwave breast imaging systems have been previously developed and clinically investigated [11]. Of these, 2 systems were considered in clinical studies with large cohorts and suggested their potential utility in the clinical settings [30,32]. These studies focused solely on sensitivity, but the diagnostic accuracy (including specificity) of these systems has not been reported. To the best of our knowledge, this study is the first of its kind that focuses on both sensitivity and specificity of a microwave breast imaging system on a per-breast basis.

Our imaging system has several advantages in addition to the general features of microwave imaging. First, it is an easy-to-operate system, where an operator simply places the device in close contact with a breast and presses a start switch. No special training is required for the examinations, and the system is not affected by differences of technical skills of its operators. Second, this system places compact integrating antennae, excitation and acquisition hardware, and signal routing in a single unit. The high portability will provide a significant benefit for remote inspection [44]. Additionally, this compact system can be used repeatedly at low cost and is useful for monitoring applications. The advantages of this system make it suitable for breast cancer screening, although concerns regarding the production of mechanical heat and influence on pacemakers need to be assessed. In the prestage experiment, the temperature of the device after 30 minutes of operation was 30 degrees, and thus the burn risk was minimal. In addition, this study will exclude individuals with a pacemaker. Therefore, the risk associated with this study is low. Data obtained in this study will be helpful for future system improvements. This study will also provide important information on factors that lead to the false positives in breast lesions and differentiation between benign and malignant lesions.

### Limitations

This study targets breast tumor cases. The diagnostic accuracy of this screening system cannot be evaluated on a per-person basis in clinical settings. In addition, the data analysts will be blind to whether breast tumors are on the left or right because of the influence of the interpretation of the test data.

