**Methods:**

This is a prospective diagnostic study. A total of 120 participants were recruited before treatment administration and divided into 2 cohorts: 100 patients diagnosed with breast cancer and 20 participants with benign breast tumors. The detector will be directly placed on each breast, while the participant is in supine position, without a coupling medium. Confocal images will be created based on the analyzed data, and the presence of breast tumors will be assessed. The primary endpoint will be the diagnostic accuracy, sensitivity, and specificity of the detector for breast cancer and benign tumors. The secondary endpoint will be the safety and detectability of each molecular subtype of breast cancer. For an exploratory endpoint, the influence of breast density and tumor size on tumor detection will be investigated.

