**Conclusions:**

This study will provide insights on the diagnostic accuracy of microwave breast imaging using a rotational bistatic impulse radar. The collected data will improve the diagnostic algorithm of microwave imaging and lead to enhanced device performance.

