### Study Population

Participants were recruited from the Hiroshima University Hospital and were classified into 2 groups: cohort 1, comprising 100 women with histologically diagnosed breast cancer; and cohort 2, comprising 20 women with histologically or radiologically diagnosed benign breast tumors.

The inclusion criteria included (1) female patients older than 20 years; (2) those with histologically confirmed breast cancer (only for cohort 1); (3) those with confirmed breast tumor by 1 or more arbitrary imaging examinations, such as mammography, breast ultrasonography, contrast-enhanced breast magnetic resonance imaging, or fluorodeoxyglucose positron emission tomography; and (4) those who provide a written informed consent. The exclusion criteria included (1) history of chemotherapy or radiotherapy within 6 months prior to registration; (2) hypersensitivity to the acrylonitrile butadiene styrene (ABS) plastic resin; (3) presence of a pacemaker; or (4) a physician’s decision. Participant examination will be discontinued and their data will be removed in case of withdrawal of consent, ineligibility, inability to participate in the study due to disease progression or complications, death, induction of treatment before the study, or any other exclusion criterion deemed necessary by the investigators. Benign breast tumors will be diagnosed by the Breast Imaging Reporting and Data System (BI-RADS) (ultrasound category 2 or less), fine-needle aspiration, or core needle biopsy. The radiological images will be read by 2 experienced radiologists.

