### Study Endpoints

The primary endpoint is the detection sensitivity and specificity for breast cancer or benign breast tumors by the screening system. Contralateral healthy breasts will also be measured in this study, and the diagnostic accuracy will be calculated on a per-breast basis. The secondary endpoints are sensitivity for breast cancer detection according to the different molecular subtypes, sensitivity for benign breast tumors according to histology, and feasibility of the examination. The biology of breast cancer will be pathologically evaluated by surgery or using collected biopsy specimens. For exploratory purposes, the influence of tumor size and breast density on the detectability of breast tumor will also be investigated.

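### Masking only the side of the tumor, when every woman has one, leaves room for left-versus-right reading that would likely overstate combined per-breast accuracy

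*Protocol article*

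**What the plan says.** Four parts of the protocol article bear on this.

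- **Masking.** Limitations: "the data analysts will be blind to whether breast tumors are on the left or right because of the influence of the interpretation". This is the only masking the article describes. The reason it gives shows that the authors recognize that prior knowledge can affect a read.
- **Population.** Study Population requires, for both cohorts, "those with confirmed breast tumor by 1 or more arbitrary imaging examinations". Limitations confirms this: "This study targets breast tumor cases". No tumor-free woman is enrolled.
- **Source of the negatives and unit of analysis.** Study Endpoints: "Contralateral healthy breasts will also be measured in this study, and the diagnostic accuracy will be calculated on a per-breast basis".
- **Primary endpoint.** Study Endpoints: "The primary endpoint is the detection sensitivity and specificity for breast cancer or benign breast tumors by the screening system".

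On how an image becomes a call, the abstract says only this: "Confocal images will be created based on the analyzed data, and the presence of breast tumors will be assessed". The article does not say whether a woman's two breasts are read together or apart, or whether the analyst knows her cohort. Limitations also concedes that "The diagnostic accuracy of this screening system cannot be evaluated on a per-person basis in clinical settings", but says nothing about bias in the per-breast figures.

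**The concern.** Hiding the side leaves a second piece of information in place: a tumor is certainly present. Anyone who knows the eligibility criteria can work out that at least one breast in each pair is positive. If the two scans can be linked to one woman, the easy question becomes which side looks worse. The question the endpoint needs is whether this particular breast contains a tumor.

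The primary endpoint is at stake. The Discussion presents joint per-breast sensitivity and specificity as the study's novelty, and Preliminary Work says that specificity is not yet clarified. A breast called negative because its partner looked worse does not show how often the device would clear a breast in a woman with two healthy ones, which is the usual situation in screening. The per-person caveat in Limitations does not cover this, because the problem lies in the per-breast estimates themselves.

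**Working it through.** **Inputs from the article.** Expected sensitivity 0.80, CI width 0.12 and 171 breasts (Sample Size Calculation); 100 women with cancer and 20 with benign tumors (Study Population).

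**Assumed, because the article gives no figure.** Specificity under separate reading, varied from 0.50 to 0.90; an equal-variance binormal image score; independence between a woman's breasts, relaxed in step 4.

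**Step 1: the planned precision.** n = z²p(1−p)/d² with z = 1.96, p = 0.80 and d = 0.06 (half of 0.12) gives 3.8415 × 0.16 / 0.0036 = 170.7, so 171. The stated figure is therefore that of a two-sided 95% interval with half-width 0.06. The stated one-sided 5% level (z = 1.645) would give 121 with the same d. Only about 100 of the 200 cohort 1 breasts carry cancer, so the half-width for sensitivity itself is nearer 1.96 × √(0.16/100) = 0.078.

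**Step 2: full forced choice, one tumor per pair.** Separate reading implies d′ = z(sens) + z(spec). If the analyst always calls the higher-scoring breast positive and the other negative, then sens = spec = Φ(d′/√2). For 0.80/0.80, d′ = 2 × 0.8416 = 1.683, d′/√2 = 1.190 and Φ = 0.883. A simulation of 1,000,000 pairs also gave 0.883. Other starting points:

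| Separate sens/spec | Forced choice, each | Sum before | Sum after |
|---|---|---|---|
| 0.70/0.70 | 0.771 | 1.40 | 1.542 |
| 0.75/0.75 | 0.830 | 1.50 | 1.660 |
| 0.80/0.50 | 0.724 | 1.30 | 1.448 |
| 0.80/0.60 | 0.781 | 1.40 | 1.561 |
| 0.80/0.70 | 0.833 | 1.50 | 1.666 |
| 0.80/0.80 | 0.883 | 1.60 | 1.766 |
| 0.80/0.90 | 0.933 | 1.70 | 1.867 |
| 0.95/0.60 | 0.910 | 1.55 | 1.820 |

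The sum rises in every row. This is general under the model: the largest sum that separate reading can reach is 2Φ(d′/2), and forced choice gives 2Φ(d′/√2), which is larger whenever d′ > 0. Sensitivity alone falls in three rows (0.80/0.50, 0.80/0.60 and 0.95/0.60). An uninformative device stays at 0.50/0.50.

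**Step 3: partial drift.** If a fraction f of pairs is read as a forced choice and the rest separately at 0.80/0.80, each measure becomes 0.80 + 0.083f. That is 0.80 at f = 0, about 0.84 at f = 0.5 and 0.883 at f = 1. The shift passes 0.06 only when f exceeds 0.06/0.083, or about 0.72.

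**Step 4: sensitivity to the assumptions.**

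- With an assumed within-woman correlation ρ, the forced-choice value is Φ(d′/√(2(1−ρ))). From 0.80/0.80 this is 0.923 at ρ = 0.3 and 0.954 at ρ = 0.5.
- With an assumed 5% bilateral rate and one positive call per woman, sensitivity is (0.95 × 0.883 + 0.05)/1.05 = 0.847.
- If cancer is the target, cohort is unknown to the analyst and all 40 cohort 2 breasts count as negative, specificity is (100 × 0.883 + 40 × 0.5)/140 = 0.774. That is below the 0.80 assumed for separate reads.

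**The case against.** The strongest reply is that the article never describes a forced choice. It does not say that side is the only thing masked, that the two breasts are viewed together, or that exactly one must be called positive. Assessing the presence of tumors and counting per breast both fit separate reads. Coding each breast file on its own would itself hide the side, so the better procedure may already be in use. Bilateral tumors are not excluded, so one call does not strictly fix the other. The article condenses a fuller protocol, where a reading rule would normally sit.

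Most of this stands. Paired reading, and the analysts' awareness that every woman has a tumor, are inferences from the eligibility criteria and the masking sentence. What the reply does not remove is that the article does fix a masking rule, and that an analyst could follow it to the letter and still exploit the pairing.

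Two stronger readings are tempting, and the document does not support either.

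- A reader might infer that sensitivity and specificity are both inflated. That is not general. From 0.80/0.60, forced choice gives 0.781 on each, so sensitivity falls, and cancer specificity can fall in cohort 2. The article gives no specificity that would settle the direction for each measure.
- A reader might infer from the abstract's Conclusions ("The collected data will improve the diagnostic algorithm of microwave imaging and lead to enhanced device performance") that the algorithm is tuned on the same data that yield the accuracy estimate. Read with the Discussion's remark on future system improvements, this describes later use. When the cut-off is locked is a matter commonly left to the full protocol or the SAP.

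**Conclusion.** The point holds as a weakness in the stated masking rule. Side-only masking, with a tumor in every woman and her other breast as the negative, lets reads drift into a left-versus-right choice. Such drift is likely to overstate sensitivity plus specificity, while either measure alone may move in either direction.

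The effect is zero if breasts are read separately. At the other extreme, with every pair a forced choice, one tumor per pair, an equal-variance binormal score and independent breasts, 0.80/0.80 appears as 0.883/0.883. That 8.3-point shift exceeds the half-width of 0.06 that reproduces the 171 breasts, and is slightly above the 0.078 that about 100 cancer breasts would give. It is the top of the range only under independence; positive correlation between a woman's breasts would raise it. The document does not show where actual practice lies, so this is a worthwhile and cheap correction, not a defect that by itself invalidates the study.

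**What to change.** Replace side-only masking with per-breast masking:

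- give each breast scan its own random code;
- remove participant identifier, side and cohort;
- shuffle the breasts of both cohorts together;
- call each breast positive or negative on its own, without access to its partner;
- report any paired left-right reading as a secondary result, labeled as such.

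If reads were already made this way, the sponsor need only say so.

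The cost is recoding and reordering stored files. Recruitment is complete and the scans exist, so no new participants, examinations or staff are needed. The downside is that left-right asymmetry, which may carry real diagnostic information, is not used in the primary read, so the figures may be less favorable.

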### Conclusions

We expect that this study will demonstrate the clinically meaningful diagnostic accuracy of the bistatic IR-UWB radar–based breast imaging system. We also hope that this study will propose a novel methodology for breast cancer screening and contribute to improvements in the current technical equipment.

## Abbreviations

ABS: acrylonitrile butadiene styrene
BI-RADS: Breast Imaging Reporting and Data System
CMOS: complementary metal–oxide–semiconductor
GMP: Gaussian monocycle pulse
IR-UWB: impulse radio ultra-wideband
MARIA: Multistatic Array Processing for Radiowave Image Acquisition
SP8T-SW: single-pole 8-throw switching matrix
